#### Analysis

***The primary outcome measure*** will be group differences in Goal Attainment Scale T-score [47] at 15 weeks post-randomisation, tested using an analysis of covariance (ANCOVA) model co-varying for Goal Attainment Scale T-score at baseline and adjusting for site as a fixed effect. Pairwise comparisons will be conducted between each of the CRT arms and treatment as usual, with significance and confidence intervals calculated using nominal values of *p*. Data will be analysed under intention-to-treat assumptions. Treatment effects for secondary outcomes will be analysed in a similar way. For the primary outcome, given the probable differences in treatment uptake (adherence), local average or complier average treatment effects compared with treatment as usual will also be estimated. Using assigned arm as an instrumental variable, all arms will be examined together to estimate the effect of hours of active CRT. On an assumption of a common per-hour effect across arms, some residual information will be available to estimate residual direct effects of treatment mode.

The ***cost-effectiveness*** analysis will be conducted from the perspectives of health and social care and society (including informal care, lost employment). Service use, collected using the Client Service Receipt Inventory, will be combined with appropriate unit cost information [64] and added to the intervention costs. Costs will be compared between groups using bootstrapped regression models to address the probable skewed distribution. Cost-effectiveness will be assessed by combining costs and outcome measures (primary outcome measure and quality-adjusted life years) in the form of incremental cost-effectiveness ratios.

If one arm has lower costs and better outcomes than another, it will be ‘dominant’. However, there will be uncertainty around the estimates of incremental costs and outcomes; this will be explored using cost-effectiveness planes and cost-effectiveness acceptability curves. The cost-effectiveness planes will be produced by generating and plotting (via bootstrapped regression models) 1000 incremental cost–outcome pairs. This will allow us to determine the probability that each arm has better outcomes and higher costs, better outcomes and lower costs, worse outcomes and lower costs, or worse outcomes and higher costs than the comparator. Cost-effectiveness acceptability curves will be generated using the net-benefit approach, whereby the incremental gain in quality-adjusted life years is multiplied by a range of threshold values for a quality-adjusted life year (including those used by NICE) and subtracting the incremental cost. This will be performed on 1000 bootstrapped incremental cost–outcome pairs and the proportion that are above zero will indicate that that one arm is more cost-effective than another. Sensitivity analyses will be conducted by varying key cost parameters. In particular, we will increase or decrease the intervention cost by 10%, 25% and 50% and use alternative methods for valuing informal care (e.g. *minimum* wage, unit cost of a homecare worker).

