### Allocation and blinding

Therapists use secure email to send a list of (11–15) consenting and assessed participants to the King’s Clinical Trials Unit, which allocates each participant using pre-generated randomisation lists. The randomised allocations are sent back to the therapist by secure email. The pre-generated randomisation lists are stored by the King’s Clinical Trials Unit in an access-restricted electronic folder that is not accessible to any members of the study team. The therapist informs each of the participants of their allocated trial arm.

Randomisation is stratified by research site in the proportion 4:4:3:4 (Group CRT, independent CRT, intensive CRT, treatment as usual) to make efficient use of therapist resources. Alternative randomisation allocations will be used if 15 participants cannot be recruited within the stipulated 12-week recruitment period, with a minimum block of 11 participants (reducing the proportions in the independent CRT and treatment-as-usual arms only so as not to break the group design constraint or reduce the number of participants in the intensive CRT arm). This flexibility allows more efficient use of therapist time and resources as the therapist time is limited and the intensive therapy absorbs a lot of this resource.

The whole team, apart from the therapists and the randomisation statistician, are blind to participant group allocation. Breaches will be recorded; if a breach is to a research assessor, another research worker will complete the assessment. An audit of the quality of the blinding will be conducted at the end of the study.

Participant data are entered online into a secure electronic data capture system hosted by the King’s Clinical Trials Unit separately from treatment allocation data. Data quality and audit are regularly tested prior to and after data entry. Analysis scripts are agreed and finalised by the senior statistician prior to unblinding.

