### Measurement

#### Power

We have the capacity to recruit 900 patients (from 1500 patients attending 10 services for 3 years) and have allowed for a 20% drop-out pre-randomisation. Using a design with parallel arms of equal size, with 180 patients per arm, provides approximately 80% power for a simple group effect size difference of 0.3. This increases to 91% for outcomes that correlate 0.5 with baseline (both calculated using sampsi in Stata).

Freidlin *et al.* [62] suggest no great advantage in accounting for multiple testing in a multi-arm trial, and also that the advantages of a larger treatment-as-usual arm are more slight than commonly assumed. Interaction among patients in group delivery is very slight so no allowance for clustering was thought necessary.

The power calculation is based on arms of equal size; the difference in power as a result of the unequal allocation is likely to be small as the use of modestly unequal randomisation ratios only very slightly reduces the power of a study [63].

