##### Interim analysis

Given that CRT is known to be effective, we want to ensure that we do not adopt all four trial arms if one treatment arm provides little benefit compared with the remainder, so we will carry out an interim intention-to-treat analysis. This will be undertaken by the health economist, using data from the first 195 patients (using the post-therapy data at 15 weeks post-randomisation). This analysis may result in one of the trial arms being closed, with an immediate impact on the randomisation of the next patients.

The decision to drop an arm will be taken by an independent data monitoring committee and will depend on the resultant cost of therapy and other services and goal attainment. The costs will include direct therapy inputs and other services derived from the Client Service Receipt Inventory.

The direct therapy costs will be calculated from data on the number and length of sessions, number of attendees (for group therapy) and unit costs, based on staff grade and overheads. Cost-effectiveness planes will be generated by plotting the 1000 incremental cost–outcome combinations for each pair of comparators. This will tell us the probability that one therapy has (i) lower costs and better outcomes, (ii) lower costs and worse outcomes, (iii) higher costs and better outcomes, or (iv) higher costs and better outcomes than a comparator.

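### The allocation ratio can change within a site and an arm may close, but the primary ANCOVA adjusts only for baseline score and site, so some contrasts with TAU can be biased

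*Protocol article*

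**What the plan says.** - **Model.** The protocol article (Analysis) specifies an ANCOVA on the Goal Attainment Scale T-score at 15 weeks, "co-varying for Goal Attainment Scale T-score at baseline and adjusting for site as a fixed effect". Each CRT arm is compared with TAU, "with significance and confidence intervals calculated using nominal values of" p. Secondary outcomes are to be handled similarly, and costs by bootstrapped regression.
- **Allocation.** Under Allocation and blinding, randomisation is stratified by site at 4:4:3:4. If 15 participants are not found within 12 weeks, smaller blocks are allowed, "with a minimum block of 11 participants (reducing the proportions in the independent CRT and treatment-as-usual arms only". How the reduction is shared between those two arms is not given.
- **Arm closure.** Under Interim analysis, 15-week data on the first 195 patients are examined. "This analysis may result in one of the trial arms being closed, with an immediate impact on the randomisation of the next patients".
- **Power.** The Power section treats unequal allocation as a small loss of power only. It does not consider bias.

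**The concern.** Randomisation makes arms comparable only among patients who faced the same allocation probabilities. Here those probabilities vary within a site: by block, according to how fast the site was recruiting, and by calendar time if an arm closes. TAU patients are then under-represented in short blocks relative to group and intensive patients. After a closure, most TAU patients would have been randomised when the closed arm was no longer available. A site main effect removes stable differences between slow and fast sites, but not differences between slow and fast periods at one site, or between early and late recruits. Any such outcome difference carries over into the affected contrasts, and into secondary and cost comparisons modelled the same way. The target effect is only 0.3 SD, so a bias of several hundredths of an SD is not trivial.

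**Working it through.** **1. The plan's own figures.** "Using a design with parallel arms of equal size, with 180 patients per arm", which "provides approximately 80% power for a simple group effect size difference of 0.3". At two-sided 5% (assumed; the level is not stated) I obtain 81.2% unadjusted and 90.8% with baseline correlation 0.5, against the stated 80% and 91%. Also 900 × 0.8 = 720 = 4 × 180. The power figures stand and are not in dispute.

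**2. Short blocks.** Assumptions, since the article gives none: an 11-patient block splits 4:2:3:2, and a fraction f of blocks is short, equally in every site.

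- Share of group patients in short blocks: 4f/[4f + 4(1−f)] = f. Intensive is the same.
- Share of TAU patients in short blocks: 2f/[2f + 4(1−f)].
- At f = 0.5: 0.500 versus 1/(1 + 2) = 0.333, a difference of 0.167.
- Bias = 0.167 × the within-site outcome difference between short and full blocks. A difference of 0.1, 0.3 or 0.5 SD gives 0.017, 0.050 or 0.083 SD.
- Independent versus TAU: both shares are 0.333, so the bias is 0.

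With splits from 4:1:3:3 to 4:3:3:1 and f from 0.25 to 0.75, a 0.3 SD difference gives 0.015 to 0.096 SD for group and intensive versus TAU. For independent versus TAU it gives up to 0.079 SD in either direction when the split is uneven.

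**3. Clustering of short blocks by site** (4:2:3:2, 0.3 SD). The site term absorbs part of the effect. With three sites at f = 0.8 and three at f = 0.2, the within-site share differences are 0.8 − 0.667 = 0.133 and 0.2 − 0.111 = 0.089. Their precision-weighted mean is about 0.11, so the bias is about 0.033 SD. At 0.9 and 0.1 it is about 0.019 SD. If each site has only one block type, it is 0.

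**4. Arm closure.** I take the closed arm to be a CRT arm. Recruitment of 720 over about 31 months (Trial status) is about 23 a month. Waiting 15 weeks (about 3.45 months) for outcomes adds about 80 patients, so closure falls between 195 (recruitment paused) and about 275. I assume TAU receives 4/15 of patients before closure, then 4/11 (a four-place arm closed) or 4/12 (intensive closed).

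Concurrent TAU share = n(4/15) / [n(4/15) + (720−n)(4/11 or 4/12)].

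| n at closure | Arm closed | Concurrent TAU | Bias, 0.2 SD step at closure | Bias, 0.2 SD linear drift |
|---|---|---|---|---|
| 195 | four-place | 0.214 | 0.157 | 0.079 |
| 195 | intensive | 0.229 | 0.154 | 0.077 |
| 275 | four-place | 0.312 | 0.138 | 0.069 |
| 275 | intensive | 0.331 | 0.134 | 0.067 |

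Step bias = (1 − concurrent share) × 0.2. Under linear drift the mean recruitment times before and after closure differ by half the recruitment span, so the bias is half the step value. If TAU instead accrued in proportion to total recruitment, a step at 195 to 330 patients would give 0.146 to 0.108 SD.

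**5. Simulation.** 720 patients, six sites, half of blocks short, baseline correlation 0.5, no treatment effect, 600 replicates (Monte Carlo SE about 0.01 on type I error).

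| Scenario | Contrast with TAU | Bias and type I error, site only | Bias and type I error, block |
|---|---|---|---|
| Short blocks 0.3 SD lower | group | −0.048, 0.087 | −0.003, 0.075 |
| Short blocks 0.5 SD lower | group | −0.083, 0.132 | −0.008, 0.053 |
| Intensive closed at about 270, linear drift 0.3 SD | intensive | −0.092, 0.118 | 0.010, 0.048 |
| Intensive closed at about 270, linear drift 0.5 SD | intensive | −0.171, 0.270 | 0.000, 0.047 |
| Group closed at about 270, linear drift 0.5 SD | group | −0.172, 0.332 | 0.005, 0.047 |

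In the first row, 600 replicates do not clearly separate the two error rates, but the biases are clearly different. In the closure runs, the arms that stayed open had biases of at most 0.004 SD with site alone.

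**The case against.** The strongest reply is that everything is conditional. Short blocks and closure are possibilities, and bias also needs outcomes to differ within a site by block type or over time. The article gives no evidence of such differences, and Goal Attainment Scale levels are set around each participant's own current and expected performance. The site term already handles differences between slow and fast sites. Closure mainly affects the arm that has been dropped. All of this stands, and it limits the size and severity of the point.

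A reader might also infer more than the documents support:

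- **That every contrast is confounded.** Independent versus TAU has no short-block bias if the two arms shrink equally, and contrasts among arms that stay open are little affected by a closure.
- **That the protocol reports care changing during recruitment.** Main challenges lists a changing NHS context, but the changes it describes are since the study was designed and already in place. It does not say that outcomes drift during the trial.
- **That any 0.2 SD drift costs 0.13 to 0.16 SD.** That needs an abrupt step at closure. Gradual drift costs half as much.
- **That the plan commits to non-concurrent TAU.** It does not say so. It simply sets no restriction.

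The argument that this belongs in an analysis plan does not hold. The article itself names the covariates and the comparator, and the objection is to that stated choice.

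**Conclusion.** The point holds in limited form and should be fixed; it does not by itself invalidate the primary analysis. The stated model does not condition on the groups within which patients are randomised.

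- **Group and intensive versus TAU.** The short-block bias is modest: about 0.05 SD, or 17% of the 0.3 SD target, under a 4:2:3:2 split, half of blocks short in every site and a 0.3 SD within-site difference. It is smaller if short blocks cluster by site.
- **A closed arm versus all TAU.** This is the larger exposure: about 0.07 to 0.08 SD (22 to 26% of the target) for a 0.2 SD linear drift, and 0.13 to 0.16 SD (45 to 52%) for a 0.2 SD step at closure.

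The mechanism follows from the text. The share of short blocks, the split, the drift and the outcome differences are all assumptions.

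**What to change.** Replace site with randomisation block nested in site as the fixed factor in the primary ANCOVA. At minimum, use site × allocation ratio × before/after arm closure. State that any closed arm is compared only with concurrently randomised TAU patients. Carry the same terms into the secondary-outcome models and the bootstrapped cost regressions.

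Cost: a change of wording, plus about 48 (720/15) to 65 (720/11) block parameters. For group versus TAU with no closure, the simulated SE goes from 0.0885 to 0.0891. For a closed arm it rises by about 7 to 10% (intensive 0.1253 to 0.1346; group 0.1128 to 0.1238), because essentially only concurrent TAU patients then inform that contrast. The article says analysis scripts are finalised before unblinding. The change should be made by then, so that it cannot look driven by the results.

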Cognitive remediation therapy is an evidence-based intervention but what is not obvious is the mode of implementation necessary and who would benefit most from different therapeutic modalities. Cognitive remediation therapies have been provided with high therapist involvement or very little, and at different intensity levels. We therefore developed the arms of the trial to represent the most frequently used implementation methods. The first is an intensive therapy that has previously been used by our team [34], which depends on continuous therapist support. The second arm is one adopted in many studies, where treatment is provided in a group with therapeutic support [35]. We have shown that our current therapy is suitable for such a group-intervention [36] approach. The final arm is one that depends on more independent access to therapy and has been used in several trials with differing effects [37, 38]. The main differences between these implementation methods is the level of therapist support and therefore the costs of implementation, with the most independent being the cheapest. Although the presence or absence of therapist support did not affect cognitive outcomes [14], therapist support has been shown to have tangible effects [39] and service users have positive views about therapists being present during therapy [40, 41]. Balancing the cost of the service, service user preferences and outcomes has not been tested as there have been no direct comparisons using the same cognitive remediation programme with differing levels of therapist support. The question of what is the best implementation method therefore has clinical equipoise. Cognitive remediation therapies have also generally been tested in single-centre studies so the effect of differing background services on outcomes has also not been tested. Therefore, this large, multicentre trial was developed, with the main aim of determining the best way of introducing CRT for psychosis into UK National Health Service (NHS) early intervention services in order to optimise individual functional outcomes and costs.

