### Trial aims and objectives

The aim is to determine the best method of introducing CRT for psychosis in UK NHS early intervention services to optimise individual functional outcomes and costs. The objectives are to compare three methods of CRT delivery on: (a) the degree to which participants have achieved their stated goals using the Goal Attainment Scale as the primary outcome measure; (b) improvement in cognition, social function, self-esteem and symptoms (the secondary outcome measures); (c) cost-effectiveness; )d) satisfaction of the service users and staff involved in the implementation.

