### Interventions

The CRT interventions (intensive, group, independent) will be carried-out using the CIRCuiTS computerised cognitive remediation programme; CIRCuiTS is based on a successful paper-and-pencil therapy and was developed with service users and therapists to increase engagement with younger clients who value computerised therapy [44, 45]. The three CRT delivery modes will differ in the associated hours of therapist contact but all participants will be offered 42 treatment hours. A treatment-as-usual arm will be evaluated, as CRT is not yet recommended in England by NICE; this will allow us to assess cost-effectiveness. All trial participants will continue to receive standard care throughout the trial.

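### Objective (a) compares the three CRT delivery methods on goal attainment, but the primary ANCOVA names only contrasts of each CRT arm with treatment as usual

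*Protocol article*

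**What the plan says.** Under Trial aims and objectives, the article states: "The aim is to determine the best method of introducing CRT for psychosis in UK NHS early intervention services". It continues: "The objectives are to compare three methods of CRT delivery on: (a) the degree to which participants have achieved their stated goals". The Goal Attainment Scale is the primary outcome, so objective (a) is a comparison between modes on the primary outcome.

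The Background gives the gap to be filled: "there have been no direct comparisons using the same cognitive remediation programme with differing levels of therapist support". Under Interventions, the TAU arm is justified by CRT not yet being recommended in England by NICE, with the remark that "this will allow us to assess cost-effectiveness".

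The Analysis section defines the primary analysis as group differences in the Goal Attainment Scale T-score at 15 weeks, "tested using an analysis of covariance (ANCOVA) model co-varying for Goal Attainment Scale T-score at baseline and adjusting for site as a fixed effect". It then names the contrasts: "Pairwise comparisons will be conducted between each of the CRT arms and treatment as usual". Tests and intervals for these are to be nominal. Secondary outcomes are to be handled similarly. The complier-average effects are also taken against TAU.

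Mode appears in two other places:
- The instrumental-variable analysis in the same section estimates residual direct effects of mode, on the assumption of a common per-hour effect across arms.
- The cost-effectiveness analysis, and the interim analysis based on it, compare arms with each other using bootstrapped cost–outcome pairs.

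**The concern.** The question and the named contrasts do not match. Objective (a) needs intensive versus group, intensive versus independent, and group versus independent. The primary analysis lists three other contrasts, each answering whether one mode beats TAU.

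This is more than detail left to a statistical analysis plan, because the article does list its contrasts and the list omits those its first objective needs. If the list is followed as it stands, the report will hold three efficacy results against TAU and no planned effectiveness estimate of how the modes differ. Between-mode estimates added later could be read as post hoc. Readers would also be tempted to rank the modes by which ones reached significance against TAU, and that ranking is unreliable.

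**Working it through.** **Inputs**
- Total 720 (Abstract, Methods).
- Allocation 4:4:3:4 for group, independent, intensive and TAU (Allocation and blinding). With full blocks this gives 720 × 4/15 = 192, 192, 720 × 3/15 = 144, and 192.
- Effect 0.3 SD, 180 per arm, power about 80%, rising to 91% with baseline correlation r = 0.5 (Power).
- Alpha is not stated as a number. I assume two-sided 0.05, which reproduces the stated power.

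**Formulae**

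SE = s × √(1/n₁ + 1/n₂), with s = 1 unadjusted and s = √(1 − 0.5²) = 0.866 with r = 0.5.
Power ≈ Φ(d/SE − 1.96); the opposite tail is negligible here.

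**The plan's own figures**
- 900 × 0.8 = 720, and 720/4 = 180.
- Unadjusted: SE = √(2/180) = 0.1054; 0.3/0.1054 = 2.846; power 81.2% (stated: about 80%).
- r = 0.5: SE = 0.0913; 0.3/0.0913 = 3.286; power 90.8% (stated: 91%).

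Both reproduce. The Power section does not say which contrast it covers.

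**Power of the missing contrasts**

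| Contrast | Difference | Unadjusted | r = 0.5 |
|---|---|---|---|
| Group v independent (192 v 192) | 0.3 SD | 84% | 92% |
| | 0.2 SD (assumed) | 50% | 62% |
| Intensive v group or independent (144 v 192) | 0.3 SD | 78% | 88% |
| | 0.2 SD (assumed) | 44% | 55% |

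For example, 192 v 192 unadjusted: SE = √(2/192) = 0.1021; 0.3/0.1021 = 2.939; Φ(2.939 − 1.96) = 0.836. For 192 v 144: SE = 0.1102; 0.3/0.1102 = 2.721; Φ(0.761) = 0.777.

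The difference detectable with 80% power is (1.96 + 0.842) × SE: 0.29 SD (192 v 192) and 0.31 SD (192 v 144) unadjusted, or 0.25 and 0.27 SD with r = 0.5.

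**Can significance against TAU stand in for these contrasts?**

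I simulated four arm means (400,000 replicates, 192/192/144/192, shared TAU arm), with every CRT mode truly 0.3 SD better than TAU, so that the modes do not differ at all.

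| | All three significant | None | Verdicts differ |
|---|---|---|---|
| Unadjusted | 63% | 4% | 33% |
| r = 0.5 | 80% | 1% | 19% |

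Between about one trial in five and one in three would therefore show a mixture of significant and non-significant modes although the modes are identical in effect.

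**The case against.** The strongest reply is that mode is not ignored. The aim is a joint one, covering functional outcomes and costs, and Trial design says that implementation methods will be compared with a net-benefit approach. The Analysis section uses the primary outcome in the incremental cost-effectiveness ratios and bootstraps the probability that one arm has better or worse outcomes than its comparator. The Interim analysis does this for each pair of comparators. Providing advice to the NHS adds satisfaction, drop-out and staff views. All four arms sit in one ANCOVA described as testing group differences, so the missing contrasts come from the same fit, and a full contrast list is often left to the analysis plan, which is not shown here.

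Much of this stands. A reader might infer that no between-mode comparison of goal attainment is planned, or that a conclusion on mode would have no inferential basis. The economic analysis rules out both readings. A reader might also infer that the best mode will be picked by significance against TAU. No section says so, and the 33% and 19% show only why that shortcut would fail. Nor is it right that the mode contrasts are badly powered at the trial's own effect size: at 0.3 SD they are close to the stated 80% and 91%.

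The core remains. A cost–outcome probability is not an effect estimate with a confidence interval. The instrumental-variable term is a mode effect net of hours under a common per-hour effect, whereas a service choosing a mode needs the intention-to-treat difference. A four-arm global test could be significant only because CRT beats TAU.

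**Conclusion.** The point holds as a mismatch between objective (a) and the contrasts named for the primary outcome. What is missing is a planned intention-to-treat estimate, with a confidence interval, of the goal-attainment difference between each pair of CRT modes. The design, the data and the stated power arithmetic are not at fault.

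The power figures rest on two-sided 0.05, full 4:4:3:4 blocks and no loss after randomisation. Loss or reduced blocks would lower them. The 0.3 SD effect and r = 0.5 are the article's own; the 0.2 SD difference is my illustration. Power is adequate if modes differ by 0.3 SD and modest, at 44% to 62%, if they differ by 0.2 SD.

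**What to change.** In the Analysis section, and in the analysis plan before unblinding:
1. Add the three CRT-versus-CRT contrasts in Goal Attainment Scale T-score at 15 weeks, from the same ANCOVA, each with an estimate and confidence interval. A 2-df test that the three modes are equal is optional.
2. State that effectiveness conclusions about the best mode rest on these contrasts, with the cost-effectiveness analysis alongside, and not on which modes differ significantly from TAU.
3. Say in the Power section which contrasts the 80% and 91% refer to, and give the power of the mode contrasts at 0.3 SD and at a smaller difference.

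The cost is wording and a little more analysis, with no extra data and no change to the design. The drawback is that the plan would then show openly that power is modest if modes differ by less than 0.3 SD.

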## Methods

### Trial design

This is a multicentre, blinded, randomised, controlled trial conducted in the early intervention services of UK NHS Mental Health Trusts. Three different methods of providing CRT (intensive, group or independent) and treatment as usual within each of six research sites will be compared on their ability to improve real-world outcomes. In addition, implementation methods will be compared on their acceptability to service users, and the cognitive, clinical and real-world outcomes and cost-effectiveness, using a net-benefit approach. The site is designed to compare different services; catchment areas of the participating trusts range from high-density inner city to suburban and so cover diverse populations and different service backgrounds. Outcomes are measured at 0 (baseline), 15 (post-treatment) and 39 (follow-up) weeks after randomisation (see Additional file 1).

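### The final cost-effectiveness acceptability curves compare arms two at a time, so they do not give the probability that a delivery mode is the most cost-effective of the four options

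*Protocol article*

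**What the plan says.** The Trial aims and objectives section states the question as a choice among methods: "The aim is to determine the best method of introducing CRT for psychosis in UK NHS early intervention services". Cost-effectiveness is one of the listed objectives. The Trial design section names four arms: "Three different methods of providing CRT (intensive, group or independent) and treatment as usual within each of six research sites will be compared".

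The Analysis section then defines the acceptability curve. Under the net-benefit approach "the incremental gain in quality-adjusted life years is multiplied by a range of threshold values for a quality-adjusted life year", and the incremental cost is subtracted. The calculation is repeated over 1000 bootstrap replicates, and its result is read in this way: "the proportion that are above zero will indicate that that one arm is more cost-effective than another". The cost-effectiveness planes have the same two-arm form, ending with the probabilities of "worse outcomes and lower costs, or worse outcomes and higher costs than the comparator".

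Nowhere does the article provide for the probability that an arm has the highest net benefit of the four at a given threshold.

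**The concern.** An incremental net benefit is a difference between two arms. The share of replicates in which it exceeds zero answers a two-option question: is A better value than B? The decision that the trial is meant to inform has four mutually exclusive options, and the relevant quantity is the probability that A is better value than B, C and D at once.

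The two can differ widely. Several modes can each score high against treatment as usual, and one mode can win every pairwise comparison, while no mode is more likely than not to be the best choice. Pairwise probabilities also do not sum to one across options, so they cannot be read as the chance that adopting a given mode is right.

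At stake is how certain the final economic result will look. Cost is a stated reason for comparing the modes (Background) and for including treatment as usual (Interventions), and the costs feed the advice to the NHS. The ranking of point estimates and the primary efficacy test are not affected.

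**Working it through.** **The plan's own figure.** The article states no number for the acceptability curves, and no costs, QALYs, variances or correlations, so there is nothing to reproduce. The checks below use assumed values.

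**Inputs from the article.** Four arms (Trial design). Pairwise rule: share of incremental net benefits above zero (Analysis). 720 participants (Abstract), allocated 4:4:3:4 to group, independent, intensive and usual care (Allocation and blinding). With full blocks that gives 720 × 4/15 = 192, 192, 720 × 3/15 = 144, and 192.

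**Assumptions.** One threshold; arm-level net benefits normal and independent. The first check takes equal variance across arms. The second takes an individual SD of 1, so each arm mean has standard error 1/√n.

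**Formulas.** With arm net benefits of mean μ and standard error s:
- Pairwise: P(A > B) = Φ[(μ_A − μ_B) / √(s_A² + s_B²)].
- Best of four: P(A best) = ∫ φ_A(x) Φ_B(x) Φ_C(x) Φ_D(x) dx, where φ and Φ are each arm's density and distribution function.

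**Check 1: modes at 95%, 90% and 90% against usual care (s = 1, μ = 0 for usual care).**
- Leader: μ = √2 × 1.645 = 2.33. Each rival: μ = √2 × 1.282 = 1.81.
- Leader against each rival: Φ[(2.33 − 1.81)/√2] = Φ(0.36) = 0.64.
- Probability of being best: leader 0.48, rivals 0.25 each, usual care 0.01.

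The leader wins all three of its comparisons (0.95, 0.64, 0.64) but is best in fewer than half of the draws. The three probabilities against usual care sum to 0.95 + 0.90 + 0.90 = 2.75.

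**What all the pairs together can tell.** Without knowing the joint distribution, the leader's three pairwise values only bound its probability of being best. It cannot exceed the smallest, 0.64, and it cannot fall below 1 − 0.05 − 0.36 − 0.36 = 0.23.

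**Check 2: how the gap varies, with arms of 192/192/144/192.** Advantages over usual care are in SD units, in the order group, independent, intensive.

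| Assumed advantage | P(better than usual care) | P(best of four) |
|---|---|---|
| 0.10 / 0.10 / 0.10 | 0.84 / 0.84 / 0.82 | 0.31 / 0.31 / 0.34 |
| 0.10 / 0.12 / 0.08 | 0.84 / 0.88 / 0.77 | 0.30 / 0.43 / 0.24 |
| 0.20 / 0.15 / 0.10 | 0.98 / 0.93 / 0.82 | 0.61 / 0.27 / 0.12 |

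In the second row, the comparisons between CRT modes run from 0.42 (group over independent) to 0.64 (independent over intensive). In the third row one mode is clearly ahead, and its probability of being best rises to 0.61.

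**The case against.** The strongest reply is that the quoted sentence is true. It says that one arm is more cost-effective than another, which is what a pairwise probability measures; it never claims to identify the best of four. The wording also allows comparisons between CRT modes, and the objectives and Trial design section point that way. Those comparisons would partly show how close the modes are: with three equal modes they would all sit at 0.50. This stands, and it lowers the risk of misreading. It does not remove the gap, because in Check 1 the leader is ahead in every pair and still best in only 48%.

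A second reply is that the sizes come from chosen inputs. This also stands. Three equal modes give about one third each by symmetry, and choosing among equals loses nothing on average.

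Two stronger readings are tempting but not supported:
- A reader might infer that the interim decision to close an arm rests on the acceptability curve. The Interim analysis section describes planes, "plotting the 1000 incremental cost–outcome combinations for each pair of comparators", with goal attainment as the outcome. It mentions no net benefit or threshold, and it asks which arm gives little benefit. Highest-net-benefit probabilities there would need a value per unit of goal attainment, which the article does not give.
- A reader might infer that the incremental ratios are wrong because no sequential ranking or extended dominance is described. The article does not fix ratios against usual care only, and such detail can be left to the full plan.

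**Conclusion.** The point holds as a mismatch between the stated question and the stated summary in the final economic analysis. The article fixes a two-option statistic where the aim is to choose among four options, and pairwise curves, even for every pair, do not supply the probability of being best.

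Under the assumptions above, a leader at 95% against usual care and 64% against each rival has about a 48% chance of being best; with a clearer leader the figure is about 61%. These values depend on the assumed net benefits, independence and variances, and the real gap could be smaller or larger.

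This is a worthwhile improvement at almost no cost. The pairwise results are not invalid, and the finding does not extend to the interim rule, the incremental ratios or the primary outcome.

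**What to change.** In the Analysis section, add that the final analysis resamples all four arms together within each of the 1000 bootstrap replicates. In each replicate, calculate every arm's net benefit at each QALY threshold. Then report, by threshold, the proportion of replicates in which each arm has the highest net benefit: four curves that sum to 1. Keep the pairwise planes and curves as supplements.

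The cost is a sentence or two of text and a small change to the analysis script. It uses the same data and the same number of replicates, and needs no further participants and no design change.
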